**EXPECTED APPLICATION OF RESULTS**

Results from the proposed study will inform programs currently implementing VMMC of the need to mount activities that would appeal to older men. The results will be shared with community leaders in study Locations and with various stakeholders in relevant forums, such as the national and provincial VMMC task-forces, and local and international meetings and conferences. In addition, findings will be shared through publications in peer-refereed journals.

**FLOW OF FORMS/APPENDICES**

**Table 7:** Summary Flow of Forms/Appendices

| **PHASE 1: HOUSEHOLD ENUMERATION** | | | |
| --- | --- | --- | --- |
| **Appendix** | | **Description** | **Purpose and flow** |
| Appendix 1: | | Household Enumeration Form – to capture information during household listing in all selected Locations/Clusters.  Obtain oral consent from the head of household or any adult member before initiating interviews | To capture: names of household heads; brief socio-demographic information; names of males age 25 – 39 years, their telephone numbers & time/day to revisit for MC ascertainment and interview; marital status; age, education level, occupation and religion of males >10 yrs.  Data manager to generate a list of eligible males and assign ID number to each – for use during revisits |
| **PHASE 2: CONDUCTING RAPID FORMATIVE STUDY** | | | |
| Appendix 4 | | Written Informed Consent for FGD with Circumcised and Uncircumcised) | Consenting circumcised and uncircumcised men for FGDs |
| Appendix 5 | | FGD Guide for Circumcised and Uncircumcised Men | To guide the conduct of FGDs |
| Appendix 6 | | Written ICF for IDI with Circumcised and Uncircumcised Men | Consenting circumcised and uncircumcised men for IDI |
| Appendix 9 & 12 | | IDI interview guide for circumcised men and partners of circumcised men | To conduct the IDIs with circumcised men and their female partners |
| Appendix 10 & 13 | | IDI Interview guide for uncircumcised men and partners of uncircumcised men | To conduct the IDIs with uncircumcised men and their female partners |
| **PHASE 3: ESTABLISHING BASELINE MC PREVALENCE AND PROPORTION OF ELIGIBLE MEN** | | | |
| Appendix 2A | | Written Informed Consent Form for Enrollment and Verification of Circumcision Status at baseline and endline | Use at post-enumeration revisit, RAs will: consent all men aged 25-39 years for enrollment; visually verification of MC status at baseline and endline. |
| Appendix 2B | | Enrollment Questionnaire and Circumcision Verification | Interview men aged 25-39 years on top reason(s) for going or not going for VMMC and verify MC status. |
| Appendix 3A | | Tracking Log. | A list of eligible men by location generated after household enumeration with information to be used for tracking them. |
| Appendix 29 | | Confidentiality Statement | For all study staff to indicate commitment to maintain confidentiality |
| **PHASE 4: IMPLEMENTING THE INTERVENTIONS** | | | |
| Appendix 14 | | Master Log | For collating enrollment information of all participants |
| Appendix 15 | | Referral Coupon | To refer eligible men for services. |
| Appendix 16 | | Toolkit for Addressing Barriers and Facilitators to VMMC | To be used for recruitment in IPC study arms |
| Appendix 18 | | DSO site information - places where s can find DSO sites in their respective Location | To guide s where dedicated VMMC services are offered |
| Appendix 17 | | MoH Approved VMMC Education Materials | To provide universal communication for recruitment for VMMC |
| Appendix 19 | | Monitoring Form for Demand Creation Strategies | To track communication strategies |
| Appendix 20A | | Written Consent Form for Two Questions With All VMMC Clients Aged 25-39 Yrs at Counseling | To consent all participants aged 25-29 years to be interviewed on motivators for VMMC. It will also be used to ask eligible males in DSO & DSO+IPC Locations seeking services in non-DSO sites why they opted for non-DSO sites.. |
| 20B | | Two Questions for All VMMC Clients Aged 25-39 Yrs at Counseling | To ask all participants aged 25-29 years 1 question to identify motivators for VMMC and 1 question to eligible males in DSO and DSO+IPC Locations seeking services in non-DSO sites To explore more about influencers of their choice for site |
| Appendix 21 | | Sample IRDO VMMC Flyer/Poster | Sample of flyer used for recruitment in all IRDO Locations which will be used in the control arms. |
| Appendix 22 | | Costing instrument | To collect information on cost of recruitment |
| Appendix 23 | | MoH VMMC Form | To extract information of eligible participants who are circumcised and identify s whose HIV status is unknown and potential for unlinked HIV testing. |
| Appendix 24: | | Written ICF for unlinked HIV testing on blood sample collected from bleeding vessels of participants whose HIV status is unknown | To obtain consent for unlinked HIV testing |
| Appendix 25: | | Sample request/delivery form | To record and track unlinked blood samples from the field to the KEMRI Lab in Kisumu |
| Appendix 26 A & B | | Procedures and SOPs for unlinked HIV testing | To be used for unlinked HIV testing of blood taken from participants with unknown HIV status. |
| Appendix 27: | | Data extraction form | To extract data from routine MoH and IRDO facilities |
| Appendix 28 | | Incident and Protocol Deviation Reporting Form | To be used for reporting any incidents or protocol deviations during the study |
| **PHASE 5: ENDLINE SURVEY** | | | |
| Appendix 2C | Written Informed Consent Form for Enrollment and Verification of Circumcision Status at endline | | To administer consent to collect end-line information during revisits to sampled households.  Endline information used to determine the number of men circumcised during the study. |
| Appendix 2B | Enrollment Questionnaire and Circumcision Verification | | Interview men aged 25-39 years on top reason(s) for going or not going for VMMC and verify MC status. |

**Table 8:** Proposed Timelines for Set Up and Data Collection

|  | **Description of activities** | **Months from Start** | | | | | | | | | | |
| --- | --- | --- | --- | --- | --- | --- | --- | --- | --- | --- | --- | --- |
|  |  | **1-3** | **4-6** | | **7-9** | | **10-12** | | **13-15** | **16-18** | **19-21** | **22-24** |
| **Start up** | Submit protocol to CDC Atlanta: CDC-DGHA Science Office; IRB. Select study locations, randomize to intervention arms. ***Up to 6 Months depending on final ethics approval*** | **x** | **x** | |  | |  | |  |  |  |  |
|  | Conduct desk review to develop messages addressing MC barriers and facilitators (use this to develop draft Demand Creation Information Tool); develop SOPs; identify local support structures, prepare logistics such as printing study materials. ***Up to 4 Months*** | **x** | **x** | |  | |  | |  |  |  |  |
| **Phase 1** | Hire and train staff, conduct household survey; visit all households with men aged 25-39 years; interview them; verify their MC status to establish MC prevalence and determine denominator. ***Up to 3 Months*** |  |  | | **x** | |  | |  |  |  |  |
| **Phase 2** | Recruit and train RAs  Conduct formative research (IDIs & FGDs).  ***1-2 Months*** |  |  | | **x** | |  | |  |  |  |  |
| **Phase 3** | Analyze information on barriers and facilitators of MC from formative phase; update and finalize Demand Creation Information Tool; submit tool to CDC and Kenyan IRBs for review and approval.  Conduct baseline interview and verification of MC status  ***Up to 3 Months unless ethics approval of modification delays***. |  |  | | **x** | | **x** | |  |  |  |  |
| **Phase 4** | Data analysis and integration of messages  Identify and train recruiters on study design and recruitment strategies.  ***Approximately 1 Month*** |  |  | |  | | **x** | |  |  |  |  |
|  | Implement the three interventions, including collecting information on costing and specimens for unlinked HIV testing. ***Approx. 9 Months*** |  |  | |  | | **x** | | **x** | **X** |  |  |
| **Phase 5** | Carry out endlline survey in all households with men 25-39 years uncircumcised at baseline; interview them; verify their MC status and use baseline data from men aged 25-39 years to determine the impact of the interventions. ***Approx. 3 Months*** |  |  | |  | |  | |  | **x** | **x** |  |
| **Cross-cutting** | Data entry, cleaning and analysis, report writing and manuscripts preparation. ***Ongoing up to 18 Months*** |  |  | | **x** | | **x** | | **x** | **x** | **x** | **x** |
|  |  | | | | | | | | | | | |
| **Sub-Study 4** | Develop SOPs; prepare logistics such as printing study materials. ***Approx. 2 Months*** |  | |  | |  | | **x** |  |  |  |  |
|  | Hire and train RAs. ***1 Month*** |  | |  | |  | | **x** |  |  |  |  |
|  | Enroll male participants in the study. ***Up to 6 Months*** |  | |  | |  | |  | **x** | **x** |  |  |
|  | Follow up male participants. ***Up to 8 Months*** |  | |  | |  | |  | **x** | **x** | **x** |  |
|  | Enroll female partners of the men in the study. ***Up to 6 Months*** |  | |  | |  | |  | **x** | **x** | **x** |  |
|  | Data entry and analysis; manuscripts preparation. ***Ongoing up to 12 Months*** |  | |  | |  | |  | **x** | **x** | **x** | **x** |

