At enrollment, participants will be given 3 months within which to go for circumcision, Participants can go whenever they want for VMMC, but our study will only capture their data if they go within 3 months. They will also be informed that a reminder of the expiry date for circumcision will be sent through text message to all participants one month before the expiry of the circumcision window period. The message will read: “***One month remaining. Take action for your health now***”. Participants will be informed at enrollment that they will be sent a text with the 3 words as a reminder that in case they have not gone for circumcision, they have 1 month remaining. This information has been captured in Written Informed Consent Form for Enrollment and Verification of Circumcision Status (Appendix 2A) as follows: **You have up to 3 months within which to go for circumcision. However, you are encouraged to go for circumcision as soon as possible; we recommend that it be within the next 3 months. Two months from now, you will be reminded through a text message to go for circumcision. The message will read: “*One month remaining.*** ***Take action for your health now*”.** The message is general and safe to receive even through a friend’s phone for those who do not own phones. A reminder is important because in an ongoing study on demand creation for VMMC in Kenya (funded by the Bill and Melinda Gates Foundation), preliminary results from the qualitative component reveal that participants who did not go for circumcision wished they were reminded because they simply forgot.

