**Inclusion/Exclusion Criteria for Baseline Phase**

Inclusion:

- Aged 25 – 39 years
- Resident of the study village - has been living in the physical structure identified during the enumeration and who has been eating together in the same household.
- Intends to continue living in the village for the next 9 months (which is the estimated duration of data collection).
- Gives written consent to participate in the study and the interventions.

Exclusion:

- Outside the age range of 25-39 years
- Non-resident of study villages
- Intends to relocate from the study village within the next 9 months
- Declines *to consent to participate in the study or the interventions*

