# PHASE 5: ESTABLISHING ENDLINE MC UPTAKE/ESTIMATING IMPACT OF INTERVENTIONS

At Endline, we will review our Participants Master Log (Appendix 14) to identify those who did not go for VMMC at the 45 VMMC clinics participating in the study. We will use the telephone numbers obtained during enrollment to contact the participants. Those who say that they got circumcised but are not in our Participant Master Log, we will make an appointment and visit them at home, or another convenient location, to administer consent (Appendix 2C), conduct Endline interview (**Appendix 2D: Phone and In-Person Interview with Uncircumcised Men at Endline**) and verify their circumcision status. Those who report not having gone for VMMC will be asked why they did not go, and their response recorded in Appendix 2D. If more than one reason is given, the participant will be asked to rank the top three reasons from most to least important. As enrolled participants go for VMMC services, we will be recording in the study’s Participants Master Log that they have been circumcised. However, only those who go for VMMC at study-designated clinics where we have stationed Research Assistants to monitor uptake will be recorded in the Participants Master Log. Recognizing that some participants could choose to go for circumcision in non-study clinics, we will need to capture those ones as well. To do this, we will not call any person apart from men who are listed in our Participants Master Log. We will review VMMC program theater registers in non-study clinics located within the 12 districts where the study is being conducted and compare the names with those indicated on the Participants Master Log as having not gone for VMMC. For those where the three names of VMMC clients in theater registers match the three names in the Participants Master Log, we will contact them using the phone numbers registered in the Participants Master Log and NOT in VMMC theater registers. When calling, the TASCO participants who could have been circumcised at non-study clinics will be asked if they were enrolled in the study. If they were, we will schedule a visit at home and obtain consent and if willing, conduct endline survey and verify MC status; if not, they will not be contacted further.

Inclusion/Exclusion Criteria

Inclusion:

- - 1. Was enrolled in the main study
    2. Resident of the study village
    3. Did not go for circumcision per TASCO Study database

Exclusion:

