**Estimated study participant accrual period**

Following a review of recruitment data from numerous studies of VMMC (IRDO program data) that we have previously conducted in several sites in the study area some of which have been selected for study implementation in this application, we estimate a conservative average study-wide combined accrual rate of 822 eligible men (25-39 years) per month across the 45 sites (18-19 men per Location per month).

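### A single calendar endline can fall up to 15 months after enrolment, although uptake is captured only for 3 months, and it drops unlogged men who have since moved

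*Protocol*

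**What the plan says.** Four parts of the protocol bear on when the outcome is collected.

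- **Window.** Phase 3: "Participants can go whenever they want for VMMC, but our study will only capture their data if they go within 3 months".
- **Residence screen.** The baseline inclusion criteria: "Intends to continue living in the village for the next 9 months (which is the estimated duration of data collection". The participant criteria under Phase 4 repeat the nine months.
- **Calendar.** Table 8 marks Phase 3, which includes "Conduct baseline interview and verification of MC status", under months 7-9 and 10-12, with the note "Up to 3 Months unless ethics approval of modification delays". Phase 5, "Carry out endlline survey in all households with men 25-39 years uncircumcised at baseline", is marked under months 16-18 and 19-21 and given roughly three months.
- **Endline method.** Phase 5: "At Endline, we will review our Participants Master Log (Appendix 14) to identify those who did not go for VMMC" at the study clinics. These men are telephoned, and those who report circumcision are visited and examined. Theatre registers at non-study clinics are searched by name. The Phase 5 criteria require residence in the study village and exclude non-residents.

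Nothing in Phase 5 ties the call to the end of a man's own three months. The Data Analysis section asks circumcised men when and where it was done, and sets no time limit on the main outcome. Table 7 describes the endline as counting circumcisions over the whole study.

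**The concern.** On the Phase 3 rule a man's outcome is settled three months after he enrols, but the protocol waits for a calendar campaign to find out what it was. Only men without a study-clinic record need that campaign. Each month of waiting can therefore lose men who did not go, or who went elsewhere, and never a man already logged. The residence rule makes the asymmetry explicit: of two men who move away in month 10, the one circumcised at a study clinic is counted and the unlogged one is excluded, although both outcomes were fixed long before.

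A second effect is on dates. Examination shows that a man is circumcised, not when it was done. For circumcisions outside study clinics, the man may have to place the event inside or outside a window that closed months earlier.

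**Working it through.** **1. The plan's own figures.** The protocol states no enrolment-to-endline interval. Its only figure that uses follow-up loss is the sample size. For 30% against 40%, two-sided alpha 0.017, 80% power and a continuity correction, n = 493 per arm. Multiplied by the design effect, 493 × 2.5 = 1,232.5, which matches 1,233. Then 1,233 × 1.30 = 1,602.9, which matches 1,603 contacted (15% refusal plus 15% loss, added). The loss allowance is one flat 15%, not linked to time.

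**2. The interval.** In elapsed months, enrolment (months 7-12) runs from 6 to 12 and endline (months 16-21) from 15 to 21.

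- Shortest gap: 15 − 12 = 3 months.
- Longest gap: 21 − 6 = 15 months.
- The last window closes at 12 + 3 = 15, just as the endline block opens. Contact is thus 0 to 12 months after a man's window closed.

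**3. Share contacted after nine months.** I assume enrolment *e* and endline contact *t* are each spread evenly. With *e* from 6 to 12, P(t − e > 9) = E[(t − 15)/6]. The mean of *t* is 18, 16.5 or 19.5 for the three endline spans, which gives 3/6, 1.5/6 and 4.5/6. The other rows follow in the same way.

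| Enrolment | Endline | Gap (months) | Mean gap | Beyond 9 months | Mean delay after window |
|---|---|---|---|---|---|
| 6-12 | 15-21 | 3-15 | 9.0 | 50% | 6.0 |
| 6-12 | 15-18 | 3-12 | 7.5 | 25% | 4.5 |
| 6-12 | 18-21 | 6-15 | 10.5 | 75% | 7.5 |
| 6-9 | 15-18 | 6-12 | 9.0 | 50% | 6.0 |
| 6-9 | 18-21 | 9-15 | 12.0 | 100% | 9.0 |
| 9-12 | 15-18 | 3-9 | 6.0 | 0% | 3.0 |
| 9-12 | 18-21 | 6-12 | 9.0 | 50% | 6.0 |

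The last four rows hold both phases to three months. Six-month enrolment is supported by the two quarters marked in Table 8 and by the accrual section ("we estimate a conservative average study-wide combined accrual rate of 822 eligible men (25-39 years) per month across the 45 sites"): 4,932 / 822 = 6.0 months. Three-month enrolment is supported by the duration note in Table 8.

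**4. Direction of the bias.** Let L, O and N be the proportions circumcised at a study clinic, circumcised elsewhere and not circumcised, with L + O + N = 1. Let a fraction *l* of the unlogged men be lost. Uptake among men with a known outcome is [L + O(1 − l)] / [L + (O + N)(1 − l)]. This exceeds the true L + O by lLN / [L + (O + N)(1 − l)], which is positive whenever L, N and *l* are.

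Illustration with O = 0 and true uptake 30%:

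- 15% of non-events lost: 0.30 / (0.30 + 0.70 × 0.85) = 33.5%.
- 25% of non-events lost: 0.30 / (0.30 + 0.70 × 0.75) = 36.4%.

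These loss fractions are assumed.

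**5. Power.** From 1,603 contacted per arm, 15% refusal, design effect 2.5 and alpha 0.05/3 (no continuity correction), loss of 5%, 15%, 25% and 30% gives power 0.84, 0.79, 0.73 and 0.69. This shows sensitivity to loss, not what the calendar would cause.

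**The case against.** The strongest reply is that the three-month limit stands in Phase 3 alone. The Data Analysis section sets no limit, Table 7 counts circumcisions over the study, the abstract speaks of a study period of up to nine months, and Table 8 runs the interventions to month 18. On those passages an endline near the end of delivery is natural. This stands as far as it goes: a reader might infer that the delay gains nothing, but that follows only from Phase 3. The longer reading does not rescue the calendar either, because follow-up would then vary from 3 to 15 months with enrolment date.

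Other objections also limit the point:

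- A reader might take 3 to 15 months as typical, or half the men beyond nine months as established. Both are scenario results. With each phase at three months the share can be none or all.
- A reader might think endline is the first re-contact. It is not. Phase 3 plans a text two months after enrolment, and Phase 4 allows up to three return visits within three months. Endline is the first *outcome* contact.
- Loss and recall are softened by telephone contact, register searches, physical verification and dates recorded at the time in study clinics. Recall concerns only the dates of off-site circumcisions, a subset of unstated size. However, the telephone does not help a man whom the residence rule excludes, and a register match still needs him to be reached.
- The delay applies to all arms, and the protocol gives no reason for it to act differently between them. With equal loss of non-events the odds ratio is preserved, though the uptake proportions that the Data Analysis section compares are not.

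**Conclusion.** The point holds as a moderate design weakness. On the Phase 3 window, the first outcome contact with unlogged men comes 3 to 15 months after enrolment at the outer limits. It falls after the screened nine months for about 25% to 75% of men with six-month enrolment and a three-month endline, and for 0% to 100% if both phases take three months. These shares assume even enrolment and contact.

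The residence rule at endline, set beside prospective logging at study clinics, makes the avoidable loss depend on outcome. Among men with a known outcome, uptake then tends to be overstated, assuming equal loss among unlogged men with and without an off-site circumcision.

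The documents support no figure for the bias, no claim that the 15% loss allowance is exceeded, and no claim that the comparison between arms is distorted in a known direction, because they give no loss rate by time or by arm.

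**What to change.** 1. Reconcile the outcome window: Phase 3 against the Data Analysis section and Table 7.
2. With the three-month window kept, start each man's endline telephone call when his own window closes. Complete it within a short grace period fixed in advance, on the same schedule in all arms.
3. Batch verification visits by village, and keep the review of non-study theatre registers as a backstop.
4. Amend the Phase 5 criteria so that no enrolled man is excluded only because he has moved. His outcome is already fixed and he can be phoned.
5. Leave the nine-month residence criterion at enrolment unchanged. A reader might infer that it could now be shortened, but the change does not need this, and the protocol ties that criterion to the duration of data collection.

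The calls and visits are the same in number, spread over more months. The cost is that endline calls run alongside late enrolment and ongoing intervention delivery. Asking men why they did not go, while neighbours' windows are open, could itself prompt some uptake. Calling by telephone and keeping one schedule in all arms limit that risk. Register review may need more than one pass.
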